## Methods

RESPOND utilises systems approaches in the design, implementation and evaluation of a large-scale intervention to prevent obesity among children aged 0–12 years. It has prospective registration as a clinical trial [31], and is a stepped-wedge cluster randomised trial in 10 communities. This protocol explains one sub-study of the RESPOND trial that relates to changes in knowledge and engagement.

The setting for the trial is the Ovens Murray and Goulburn regions of north eastern Victoria, Australia Fig. 1, which covers a population of approximately 30,000 children (aged 0–12 years) [32]. For the purpose of trial design, communities are defined as local government areas (LGAs), which are the geographical divisions administered by municipal governments within Australian states and the Northern Territory [33]. The unit of randomisation and intervention (clusters) is the LGA (rather than individual children or townships). The ten LGAs will be ranked in order of population size and divided in five pairs. A computer-generated random list will be generated by the study statistician who will not be involved with any aspect of the enrolment process and has no contact with the communities. One community from each pair will be randomly allocated to receive the intervention at step 1. Blinding is not feasible in this trial as the whole community is recruited into the design, implementation and evaluation.

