**Fig. 2 Fig2:**
[figure not shown]
The RESPOND Governance Structure

The number of possible participants will be used as the denominator and is based on maximum possible participation across all tiers of the governance structure and implementation teams (Table 1).

**Table 1 Tab1:** Sampling frame: groups and estimated maximum respondent numbers per community

Governance groups	Members	Number of groups	Estimated* maximum possible participants per group	Estimated* maximum possible number of responses per time point	Proposed timelines
Regional Partners Group (RPG)	Signatories to the funded grant	1	44	44	Feb/Mar 2019–2023
Regional Implementation Network (RIN)	One prevention staff member from each community (*n* = 10)	1	10	10	Feb/Mar 2019–2023
Community Action Groups (CAG)	Participants of three workshops and community-led strategies	10	100	1000	Feb/Mar 2019–2023

*Estimated maximum participant numbers based on the current number of 12 partner organisations which may increase or decrease throughout the life course of the grant

Including baseline, for the Knowledge and Engagement Survey, there are five data collection points over the 5-year period of the grant in step 1 communities, and three data collection points in step 2 communities (this survey is administered annually). It is theoretically possible that a maximum of 4270 observations could be collected.

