### Outcomes

The SDCD will measure levels of knowledge and engagement prior to commencement, during intervention (annually, 2019–2023) and at the end of the intervention (2023). The Regional Partners Group and Implementation Network will be surveyed at all five time points, while the community-specific Community Action Groups will be surveyed annually from the time the groups come into existence post GMB 3 (2019 for step 1, 2021 for step 2).

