### Data management and analysis plan

The responses to each SDCD survey question will be coded from 0 (strongly disagree) to 1 (strongly agree) [0 = 0 strongly disagree, 0.25 = disagree, 0.50 = agree, 0.75 = agree, 1.00 = strongly agree]. Domain summaries are the average of items within each domain. Participant summaries are averages of the domains (domain-weighted rather than item-weighted). We view the domains as equally important as each other, and the number of items is not related to how important the domains are, rather the complexity of eliciting the information about each domain. The SDCD survey will be summarised at participant level as the average of items within each of the five domains of knowledge (5 knowledge sub-scores) and the five domains of engagement (5 engagement sub-scores) (see Table 3).
*Analysis*: RQ1: What is the baseline level of community leaders’ knowledge and engagement in each of the governance and implementation groups within the project and how does it differ between communities?

Variability of scores and sub-scores of knowledge and engagement at baseline across participant communities will be estimated based on surveys completed by participants in the Local Implementation Groups. Of note, ‘baseline’ corresponds to the 2019 survey for step 1 communities and to the 2021 survey for step 2 communities. Variability across communities will be estimated using a linear mixed model (multi-level) with community as the random factor.
*Analysis*: RQ2: How do levels of knowledge and engagement among community leaders change during participation in a whole-of-community systems intervention?

We will fit linear mixed models with time as fixed effect and participant as random effect (to account for the repeated measurements) to assess whether a temporal trend exists in the SDCD scores (and sub-scores) and whether the intervention induces changes in trends of SDCD scores. For Regional Implementation Network participants/communities, the model will further include community allocation to step 1 or 2 as fixed effect, and the breakpoint (2021) to allow for changes in slope in step 2 communities. For Local Implementation Groups, the model will additionally include community as a random effect to account for clustering. If for any participant group a linear relation between a given score and time is not supported by the data, time will be incorporated as a categorical variable.

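### As specified, the Regional Implementation Network model gives both steps one shared 2019–2021 slope, so its step 2 slope change does not estimate the intervention's effect on trend

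*Protocol article*

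**What the plan says.** The data management and analysis plan, under RQ2, states the base model for all tiers: "We will fit linear mixed models with time as fixed effect and participant as random effect". Its purpose is to assess whether a temporal trend exists and "whether the intervention induces changes in trends of SDCD scores". For the Regional Implementation Network the model further includes "community allocation to step 1 or 2 as fixed effect, and the breakpoint (2021) to allow for changes in slope in step 2 communities". If a linear relation with time is not supported for a participant group, "time will be incorporated as a categorical variable". No step-by-time term, no exposure-time term and no step 1 breakpoint is named.

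The Methods section says of allocation: "One community from each pair will be randomly allocated to receive the intervention at step 1". Under Outcomes, "The Regional Partners Group and Implementation Network will be surveyed at all five time points", whereas the Community Action Groups are "surveyed annually from the time the groups come into existence post GMB 3 (2019 for step 1, 2021 for step 2". Table 1 describes the network's members thus: "One prevention staff member from each community", ten in all.

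**The concern.** The network is the only tier observed before intervention in communities still waiting for it. Action groups are first surveyed once they exist, and the partners group is a single regional body with no step. Any controlled answer on the intervention's effect on trend must therefore come from this model.

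Between the 2019 and 2021 surveys, five communities are under intervention and five are not. Their slope difference in that period is what randomisation provides. A single time slope with a step main effect lets the two steps differ in level but not in slope before 2021. The common slope then absorbs much of the intervention effect from step 1, and the step 2 breakpoint is measured against that contaminated slope. A reader would naturally take the step 2 slope change as the intervention's effect on trend, and it could carry the wrong sign. Change in overall knowledge and engagement across the three tiers is a primary outcome of this sub-study.

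**Working it through.** **The article's own figure.** It gives no power, effect size or variance for this model. Its one total, the maximum number of observations, reproduces from Table 1 and the stated survey counts: 44×5 + 10×5 + 500×5 + 500×3 = 220 + 50 + 2500 + 1500 = 4270. The network supplies at most 50 of these (1.2%).

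**Inputs.** Five communities per step (Methods), one network member each (Table 1), five annual surveys (Outcomes), and starts in 2019 and 2021 (Outcomes and Trial status).

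**Assumptions not in the article.** The effect is a constant added slope delta, equal in both steps; the 2019 survey precedes exposure in step 1; response is complete.

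**Notation.** t = year − 2019 = 0,1,2,3,4, and k = max(0, year − 2021) = 0,0,0,1,2. Years under intervention are t in step 1 and k in step 2. With balanced data the expected coefficients do not depend on the intraclass correlation (checked at 0, 0.3 and 0.7), so least squares on values centred within step suffices. The sums of squares and products within one step are Σt² = 10, Σtk = 5, Σk² = 3.2.

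**1. Stated terms, linear time.** Let b1 be the common slope and b3 the step 2 slope change. The normal equations have left sides 20·b1 + 5·b3 and 5·b1 + 3.2·b3, with determinant 20×3.2 − 5² = 39.
- Intervention slope delta, no secular trend: right sides are 10 + 5 = 15 and 3.2. Then b3 = (20×3.2 − 5×15)/39 = −11/39 = **−0.28 delta**, and b1 = (15×3.2 − 5×3.2)/39 = 32/39 = 0.82 delta.
- No effect, slope change kappa in both steps at 2021: right sides are 5 + 5 = 10 and 3.2. Then b3 = (64 − 50)/39 = 14/39 = **+0.36 kappa**.
- No effect, linear secular trend only: b3 = 0.
- Uptake one year late in both steps: right sides are 8 + 2 = 10 and 1.4, so b3 = (28 − 50)/39 = −0.56 delta. The reversal does not hinge on exact start dates.

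**2. Stated terms, categorical time.** Common year effects cancel in the step 2 minus step 1 difference, which is delta×(0, −1, −2, −2, −2). Regressing this on k gives −1.8/3.2 = **−0.56 delta**. A shared 2021 change gives 0.

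**3. Step-by-time read in.**
- Linear time: step 2 has its own intercept, slope and kink, so b3 = 1.00 delta. A shared 2021 change returns **+1.00 kappa**, because step 1 has no breakpoint.
- Categorical time: the difference in (2) equals −t + k, so b3 = 1.00 delta, and a shared change gives 0.

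**4. Common calendar time + step + years under intervention.** The exposure difference between steps is e = (0, −1, −2, −2, −2), so the coefficient is 1.00 delta, and 0 under a shared 2021 change. The same holds with linear time and a 2021 break in both steps.

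**Precision** (residual variance σ², five members per step). Stated model: Var(b3) = (σ²/5)×20/39. Proposed model: centred Σe² = 13 − 5×1.4² = 3.2, so the variance is (σ²/5)×2/3.2. The ratio of standard errors is √(0.625/0.513) = 1.10. For step-by-time with categorical time, Σk² net of t is 3.2 − 5²/10 = 0.7, and the standard error is √(3.2/0.7) = 2.1 times that of the proposed model.

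**The case against.** The sign reversal rests on a literal reading. The article gives one sentence and no equation, and a step-specific change in slope often goes with step-specific slopes. If step-by-time was meant, delta is recovered under a linear secular trend. If the categorical fallback then also applies, a shared 2021 change does no harm. This stands: a reader might infer that the network model cannot recover the effect on any reading, and the text does not support that. Two things remain. The sentence lists its terms and the interaction is not among them. And the fallback depends on non-linearity being noticed in at most 10 members, or 6 to 7 at the anticipated 65% response, which is unlikely.

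The remedy also has limits. Its 1.00 delta follows from generating and fitting the same linear-in-exposure form. If scores rise by one unit in the first year and then plateau, the step difference is (0, −1, −1, 0, 0) and the exposure coefficient is 0.2/3.2 = 0.06. Under that pattern the stated model gives (20×1.8 − 5×5)/39 = +0.28, so the reversal belongs to a sustained slope effect. The network is also described under Participants as a forum for sharing experience among communities. If step 2 members gain at half the rate before 2021, the exposure coefficient is 0.5 delta. These are assumptions to state; they do not favour the listed terms.

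Finally, RQ2 and the primary outcome ask about change over time, and no coefficient is named as the intervention effect. That limits the weight of the point. But the RQ2 analysis does set out to assess change induced by the intervention, and only this tier is given terms for it.

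**Conclusion.** The point holds for the terms as listed. Under a constant added slope, the step 2 slope change is expected to be −0.28 delta (linear time) or −0.56 delta (categorical time) instead of +1.00 delta, and the linear model returns +0.36 kappa when there is no effect but a shared 2021 change. With step-by-time read in, the remaining weakness is narrower: a shared 2021 change is credited to the intervention unless the fallback is invoked. The figures rest on an equal, constant yearly gain in both steps, no exposure in step 2 before 2021, and complete response.

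A reader might go further and conclude that the sub-study's primary outcome, or the trial, is invalidated. The documents do not support that. This is one tier of at most 10 members by Table 1, precision will be low under any model, and the BMIz outcome is untouched.

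**What to change.** For the Regional Implementation Network, state the model as: calendar time common to both steps (categorical year, or linear time with a 2021 break in both steps) + step + years under intervention (step 1: year − 2019; step 2: max(0, year − 2021)) + participant random effect. Name the coefficient on years under intervention as the intervention's effect on trend. State that it assumes a constant yearly gain and that step 2 members are not exposed through the network before 2021. No further covariates are needed in so small a group. If step-by-time was intended instead, say so and put the 2021 break in both steps.

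Describe the partners group and action group results as uncontrolled time trends, without attributing change to the intervention.

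The cost is analysis wording and a standard error about 10% larger than under the stated model. Data collection is unchanged.

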**Discussion:**

We hypothesise there will be heterogeneity between intervention sites on levels of knowledge and engagement and that these differences will be associated with variability in implementation success.

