#### Primary outcomes

Baseline overall knowledge and engagement scores across the three levels of governance: Regional Partners Group, Regional Implementation Network and Community Action Groups.Change in overall knowledge and engagement since baseline across the three levels of governance.

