*Analysis*: RQ3: Explore whether average community baseline knowledge and engagement levels and/or average community changes in knowledge and engagement levels are associated with implementation effectiveness of system-level intervention.

For each community, data on knowledge and engagement of community leaders at baseline and changes in knowledge and engagement will be summarised using location and dispersion measures. We will explore whether these measures are associated with implementation effectiveness (number of actions implemented by the community) using nonparametric correlation and if appropriate linear models.

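### The RQ2 model for the local community groups, as ordinarily read, lets communities differ in level but not in trend, so the uncertainty of the average change is understated if community trends differ

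*Protocol article*

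**What the plan says.** The section 'Data management and analysis plan' sets out the RQ2 analysis term by term. The base model is linear mixed, "with time as fixed effect and participant as random effect (to account for the repeated measurements". For the Regional Implementation Network it adds step allocation and "the breakpoint (2021) to allow for changes in slope in step 2 communities". For the local groups it says: "For Local Implementation Groups, the model will additionally include community as a random effect to account for clustering". If a linear trend does not fit, "time will be incorporated as a categorical variable". No random slope or community-by-wave effect is named for either form of time.

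The second primary outcome is "Change in overall knowledge and engagement since baseline across the three levels of governance". The Methods section makes the local government area the unit of randomisation and intervention. RQ3 then asks whether "average community changes in knowledge and engagement levels are associated with implementation effectiveness".

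The name Local Implementation Groups is not among the three groups described under 'Participants'. I read it as the 10 Community Action Groups.

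**The concern.** A community random intercept handles the correlation that arises because some communities score higher than others throughout. It does not handle correlation in change. If each community has its own trend, all respondents in that community share the same departure from the average trend, and more respondents do not average that departure out. A model without a community-by-time term puts almost none of this variation into the standard error of the trend. The reported precision then follows the number of respondents, when it should be limited by 10 communities.

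The plan's own structure makes differing trends plausible. Each community designs and leads its own actions, and RQ3 takes each community's average change as a possible predictor of implementation. That predictor carries information only if the changes differ. At stake is the precision claimed for a primary outcome at one of the three governance levels.

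**Working it through.** **Inputs from the article.** There are 10 communities, five per step. Step 1 communities have five waves and step 2 communities three. The sampling frame is at most 100 people per community group, with an expected 40% response, so about 40 respondents per community per wave.

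**Check of the design.** The article's maximum number of observations reproduces: 44×5 + 10×5 + 5×100×5 + 5×100×3 = 220 + 50 + 2500 + 1500 = 4270.

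**Assumptions (not in the documents).** Participant SD and residual SD are each 0.10 on the 0 to 1 score. Respondents per community per wave, n, are 20 or 40. The sample is either a full cohort or entirely new respondents at each wave. The SD of community slopes, τ, is 0 to 0.010 per year. For scale, 0.010 per year is 0.04 over four years, and one step between adjacent response categories is coded 0.25. Time is linear, with a fixed step term and balanced waves.

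**Formulae.**
- Sum of squares of time: 10n in a step 1 community, 2n in a step 2 community; total 5×10n + 5×2n = 60n.
- Reported variance of the slope: V0 = v/(60n). Here v = 0.10² = 0.01 for a full cohort, and 0.10² + 0.10² = 0.02 for new respondents.
- Variance left out: B = τ² × [5(10n)² + 5(2n)²]/(60n)² = τ² × 520/3600 = 0.1444τ². This does not depend on n. It equals τ²/6.9, so the slope rests on about 6.9 effective communities however many people respond.
- Ratio of true to reported standard error: R = √(1 + B/V0). Two-sided type I error at nominal 5%: 2Φ(−1.96/R).

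The small part of the slope variance that the fitted residual absorbs is ignored.

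**Numbers.** B is 9.03×10⁻⁷, 3.61×10⁻⁶ and 1.444×10⁻⁵ at τ = 0.0025, 0.005 and 0.010.

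| Scenario | V0 | τ = 0 | τ = 0.0025 | τ = 0.005 | τ = 0.010 |
|---|---|---|---|---|---|
| n = 40, full cohort | 4.17×10⁻⁶ | 1.00 (5%) | 1.10 (8%) | 1.37 (15%) | 2.11 (35%) |
| n = 20 full cohort, or n = 40 new respondents | 8.33×10⁻⁶ | 1.00 (5%) | 1.05 (6%) | 1.20 (10%) | 1.65 (24%) |
| n = 20, new respondents | 1.67×10⁻⁵ | 1.00 (5%) | 1.03 (6%) | 1.10 (8%) | 1.37 (15%) |

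Each cell gives R, with type I error in brackets.

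**Check by simulation.** Fitting the intercept-only model to simulated data (n = 40, full cohort, community intercept SD 0.03, 199 usable replicates per scenario) gave type I error of 5.5%, 18% and 37% at τ = 0, 0.005 and 0.010. This agrees with the first row.

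**Sensitivity to the SD.** At τ = 0.010, full cohort and n = 40, a residual SD of 0.15 gives V0 = 0.0225/2400 = 9.375×10⁻⁶ and R = √(1 + 1.54) = 1.59. At n = 10 with the same SD, V0 = 3.75×10⁻⁵ and R = √(1 + 0.385) = 1.18. With both SDs at 0.15, n = 20, new respondents and τ = 0.005, V0 = 0.045/1200 = 3.75×10⁻⁵ and R = √(1 + 0.096) = 1.05.

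**The case against.** The strongest reply is that the text says random effect, not random intercept, and rules nothing out. The article is condensed, and covariance structures and small-sample corrections are often settled in an analysis plan, which is not shown here. That is fair as far as it goes: an unseen plan could add the slope. But the article does list the random effects, and anyone fitting what it lists would fit intercepts only. It is also unclear whether the step term and 2021 breakpoint carry over to the local groups. If they do, they are fixed effects, and communities within a step still share one trend.

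The size is also open to challenge. No SD, intraclass correlation, slope variance, retention or alpha is given. With equal community slopes there is no understatement, and with few respondents, noisy scores or low retention it is slight. This stands, and the point must be put conditionally.

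Two stronger readings are not supported:
- A reader might cite the expectation that "there will be heterogeneity between intervention sites on levels of knowledge and engagement" as evidence of differing trends. That statement concerns levels (the Introduction specifies baseline levels), which a community intercept already models. RQ3 is the relevant text, and it is exploratory: it allows for differing changes without asserting them.
- A reader might infer that the move from linear to categorical time inflates the error of the trend test. The article says only that linearity "is not supported by the data, time will be incorporated as a categorical variable"; it sets no formal linearity test. A figure such as 8.1% needs an assumed 5% linearity test and counts rejections by a different, overall test of time. A pre-stated fallback of this kind is ordinary practice.

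**Conclusion.** The concern holds in conditional form. As ordinarily read, the RQ2 model for the local groups has no term for communities changing at different rates, while RQ3 allows for exactly that. If trends differ, the standard error of the average trend is too small and its test over-rejects. The direction is the same in every scenario with unequal slopes; the size ranges from negligible to about a factor of two over the assumed values tabulated above, and cannot be fixed from the documents.

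The point does not extend to the Regional Partners Group, which is a single group, or to the main trial's BMIz outcome. Nor does it show that the reported precision will in fact be wrong, since the true slope variation is unknown.

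**What to change.** For the local groups, state that the RQ2 model includes participant and community random intercepts and a community random slope for time since baseline, with small-sample degrees of freedom such as Kenward-Roger. If time is categorical, replace the slope by a community-by-wave random effect. State the fallback if the fit fails to converge or is singular, for example an uncorrelated intercept and slope, or an analysis of community-level changes. Use one name for the local groups throughout.

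The cost is wording, plus wider intervals where slopes differ. With n = 40, a full cohort and residual SD 0.10, the variances of one community's slope are 0.01/400 = 2.5×10⁻⁵ (step 1) and 0.01/80 = 1.25×10⁻⁴ (step 2). Weighting each community by 1/(τ² + that variance) gives a standard error of 0.0027 at τ = 0.005 and 0.0040 at τ = 0.010, against about 0.0020 reported by the intercept-only model. With a multiplier of 2.26 on about 9 degrees of freedom (10 − 1, an upper limit) in place of 1.96, the 95% half-width goes from 0.0040 to about 0.0062 or 0.0091 per year. If slopes are equal, the standard error is unchanged and the cost is mainly the larger multiplier. With only 10 communities, boundary fits are likely at times; trial random-slope fits to simulated data often gave such warnings, so the fallback is needed.

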#### Secondary outcomes

Changes in knowledge and engagement sub-scales over time since baseline across the three levels of governance between 2019 and 2023.Association between baseline and/or changes in knowledge and engagement with the type and level of community-led actions matched against the variables and connections identified in the causal loop diagrams created. For example, active travel as a variable may result in specific actions such as the construction of bike storage or bus drop-off zones to improve active travel.

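### RQ3 pools communities with about 4 and about 2 years of follow-up and has no common window, rate or step term, so step can confound the link between score change and number of actions

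*Protocol article*

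**What the plan says.** The RQ3 paragraph of the Data management and analysis plan defines implementation effectiveness as a count and names the method. Community baseline scores and changes are to be examined for whether they are "associated with implementation effectiveness (number of actions implemented by the community) using nonparametric correlation and if appropriate linear models". On the other variable it says that "changes in knowledge and engagement will be summarised using location and dispersion measures". It gives no end date for the action count, no horizon for the change, no rate or offset, and no term for step.

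The design makes follow-up unequal:

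- Methods: ten communities form five pairs, and "One community from each pair will be randomly allocated to receive the intervention at step 1". That gives five communities in each step.
- Data management and analysis plan, RQ1: baseline "corresponds to the 2019 survey for step 1 communities and to the 2021 survey for step 2 communities".
- Outcomes: Community Action Groups are "surveyed annually from the time the groups come into existence post GMB 3 (2019 for step 1, 2021 for step 2").
- Participants, below Table 1, on the number of waves: "five data collection points over the 5-year period of the grant in step 1 communities, and three data collection points in step 2 communities".
- Secondary outcomes: "Changes in knowledge and engagement sub-scales over time since baseline across the three levels of governance between 2019 and 2023".

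Elsewhere the plan does recognise step. The RQ2 model for the Regional Implementation Network has step allocation as a fixed effect and a breakpoint at 2021. RQ3 carries over neither.

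**The concern.** A count of actions grows with the time over which it is counted. A change since baseline also grows with time, provided scores trend. If both run to 2023, step 1 communities have about twice as long as step 2 communities to accumulate each. Step then acts as a common cause of the two variables, and a correlation over all ten communities mixes any true association with the effect of exposure time.

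RQ3 is where the plan examines its hypothesis that differences in knowledge and engagement go with implementation success. With ten communities in two equal exposure groups, an artefact of step can form a large part of the observed correlation.

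The baseline-score part of RQ3 is affected differently. A baseline score does not accrue with follow-up, so there is no shared growth. The action count still varies by step for a reason unrelated to knowledge or engagement. That adds noise, and it can bias the result in either direction if baseline scores measured in 2021 differ systematically from those measured in 2019.

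**Working it through.** **Step 1: confirm the imbalance from the plan's own figure.** Inputs from Table 1: 44 Regional Partners Group members, 10 Regional Implementation Network members, and 10 Community Action Groups of up to 100. Five groups have 5 waves and five have 3.

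- Regional groups: (44 + 10) × 5 = 270
- Step 1 action groups: 5 × 100 × 5 = 2500
- Step 2 action groups: 5 × 100 × 3 = 1500
- Sum: 270 + 2500 + 1500 = 4270, which is the stated maximum

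Five annual waves span 4 intervals and three span 2. So the exposure ratio is 4 : 2 if both quantities run to 2023.

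**Step 2: change–actions part, with no association within step.** The documents give no action rates, score trends or variances, so everything here is assumed. Let T = 4 for five communities and T = 2 for five.

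- Change = slope × T + noise, with between-community SD 0.03 or 0.05 on the 0–1 score scale.
- Actions are Poisson with mean 10 × T × a community rate factor, whose CV is 0.3 or 0.6. Expected counts are 40 and 20.
- Spearman correlation, n = 10, critical |rho| 0.648 (two-sided 5%; about 2.4% in the upper tail), 20,000 runs per scenario.

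| Score trend per year | Mean rho | P(rho ≥ 0.648) |
|---|---|---|
| −0.02 | −0.17 to −0.41 | 0% to 0.6% (lower tail 7% to 21%) |
| 0 | about 0 | 2.1% to 2.4% |
| +0.01 | 0.09 to 0.23 | 4% to 9% |
| +0.02 | 0.17 to 0.41 | 7% to 21% |
| +0.03 | 0.25 to 0.53 | 10% to 36% |
| +0.05 | 0.35 to 0.61 | 16% to 51% |
| Gain stops after year 2 | about 0 | 2.5% |

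A second set-up used lognormal action rates (CV 0.3 or 0.5), slopes of 0.02 or 0.03 with SD 0.01 or 0.02, and measurement noise SD 0.02. It gave mean rho 0.16 to 0.47 and two-sided rejection of 6% to 28%. Over slopes of 0.02–0.03 the two set-ups together span about 0.16 to 0.53.

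**Step 3: upper limit.** Suppose step separates both variables completely, with random order within step. The variance of ranks 1–10 is (100 − 1)/12 = 8.25. The part between the two halves is 2.5² = 6.25. Expected rho is 6.25/8.25 = 0.76, and 90% of simulated runs exceed 0.648.

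**Step 4: baseline-score part.** Assumptions: 10 actions per year, rate CV 0.3 or 0.5, true latent correlation 0.8, no step difference in baseline scores. Using counts over unequal time instead of actions per year lowers power from 49% to 19% (CV 0.3) or from 62% to 37% (CV 0.5). With no true association but baselines differing by 1 SD between steps, the false-positive rate is 10% to 15%, with sign following the direction of the difference.

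**Step 5: do the alternatives remove it?** For the change–actions part:

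- Common 2-year window: mean rho about 0 and two-sided rejection about 5%.
- Ranking within step: mean rho about 0.
- Per-year rates: mean rho about 0 and rejection about 5%, but only because accrual was simulated as linear or only the score levelled off. If scores and actions both stop growing after year 2, step 1's per-year values are 2/4 = half of step 2's on both variables, which produces a positive correlation again.
- Separate tests within each step: with n = 5 there are 120 orderings. Rho = ±1 has p = 2/120 = 0.017, and the next value, ±0.9, has p = 10/120 = 0.083. Only a perfect ordering reaches p < 0.05.

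**The case against.** The strongest case on the other side is that the text does not say the changes are endpoint differences to 2023, or that actions are counted to 2023. The only change model described, in RQ2, has time as a fixed effect, so a community's change could be a slope. The linear models allowed in RQ3 could carry a step term. Window and scaling are also details that an article may leave to an analysis plan. This stands in part: the change horizon and the action cut-off are inferences. What the article does fix is the effectiveness measure, a plain number of actions, and an unadjusted correlation as the lead method. Followed as written, the count mixes two exposure times.

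A reader might infer that RQ3 necessarily creates a spurious positive association, or that a positive result could not be interpreted at all. The documents support neither. The plan states no direction for the score trend, and RQ2 asks whether there is one. With flat or plateauing scores there is no bias in the change part, and with falling scores it is negative. The shared-growth mechanism does not reach the baseline part, which the stated hypothesis chiefly concerns. Rising scores are a natural expectation where leaders are trained and engaged, but that is an expectation and not an input from the plan.

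It is also fair that RQ3 is explicitly exploratory, that the association is a secondary outcome, and that no alpha or decision rule is attached to it. The false-positive rates above are therefore a yardstick, not a breach of a stated error rate. No primary outcome is touched.

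**Conclusion.** The point holds in a limited form. The 4-versus-2-year split is certain from the stated waves and baselines, and RQ3 names nothing to handle it. If actions and changes run to 2023, step confounds the change–actions correlation, with a sign that depends on the score trend after year 2. In the baseline part the main effect is lost power, with possible bias in either direction if baselines differ by step.

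The size rests wholly on assumed inputs. For scores rising 0.02–0.03 per year and 10 actions per year, mean spurious rho is about 0.16 to 0.53. At the weak end the inflation is slight (two-sided rejection of about 6% against 5%). At the strong end more than a third of null data sets (36%) would exceed the upper critical value. Because RQ3 is exploratory and secondary, this should be fixed before analysis but is not a critical flaw.

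**What to change.** In RQ3, state one window for both variables. As the main version, count actions and measure score change over the first 2 years from each community's own baseline: 2019–2021 for step 1 and 2021–2023 for step 2. Use the same 2-year action count in the baseline-score part.

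Add a sensitivity analysis over all follow-up, using a correlation partial on step or pooled within-step ranks, rather than separate tests in five communities each. Actions per year and change per year can be shown as a supplementary version, with the note that they assume linear accrual.

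The cost is analysis wording only, with no new data. The main version sets aside step 1 data after 2021. At maximum participation that is two waves in five action groups, 5 × 100 × 2 = 1000 of the 2500 + 1500 = 4000 possible action-group responses, plus any step 1 actions after 2021. The sensitivity analysis brings these data back.
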